### Participant timeline {13}

Table 1 shows the schedule of assessments.

**Table 1 Tab1:** Schedule of assessments

	**Screening**	**Treatment phase**		**Follow-up**	**Final visit**
**Visit no:**	1	2	3	4	5
	Screening and baseline assessment	4-month follow-up	8-month end-of-treatment follow-up	11-month follow-up	14-month (6 months post-treatment) follow-up
**Window of flexibility for timing of visits:**	n/a	+ 2 months	+ 3 months	+ 2 months	+ 3 months
**Informed consent**	YES				
**Eligibility confirmation (CIS-R and DJG measures)**	YES				
**Intervention credibility measure**	YES				
**All outcome measures and service user information listed in s. 10.1**	YES		YES		YES
**Depression (PHQ-9) and Loneliness (ULS-8) measures only**	YES	YES		YES	
**Randomisation**	YES				
**Trial intervention/treatment**		YES	YES		
**Adverse events active monitoring**	YES	YES	YES		
**Adverse events review**	YES	YES	YES	YES	
**Withdrawal**	YES	YES	YES	YES	YES

### Sample size {14}

We will recruit 306 participants. The standard calculation to detect a 0.4 standard deviation (sd) difference in PHQ-9 depression score between arms with 90% power and 5% alpha requires 132 participants per arm. Adjusting for baseline PHQ reduces the sample size by *r*-squared, where *r* is the correlation between baseline and follow-up outcome values [38]. Assuming a correlation of 0.5 and 15% attrition (informed by the feasibility trial [7]) results in a sample size of 117 participants per arm. Assuming four sites, three navigators per site, and an ICC for clustering by navigator of 0.05, results in a design effect of 1.6 (based on 13 participants per navigator). Inflating the sample size for clustering in the intervention arm only (to 188), then adjusting group sizes to be equal, produces a sample size of 153 participants per arm.

In response to peer review comments, we have checked the sample size calculation using simulation and have found that we do obtain 90% power, as calculated, when analysing the data using a mixed model with ML, treating each control subject as a cluster of size 1. However, as noted by the reviewer, the confidence interval coverage and type I error are slightly improved by analysing the data using REML with the Kenward-Rogers adjustment. This results in a slight loss of power but is the analysis we now intend to use. The power to detect a (standardised) difference of 0.4 is reduced to 87%, or equivalently, we have 90% power to detect a difference of 0.42. This still provides 90% power to detect a minimum personally meaningful difference on PHQ-9 between groups of about 2 points [39].

### Recruitment {15}

Study researchers will regularly visit participating clinical teams, attend team meetings and arrange individual meetings with clinicians. We will seek help from all involved clinicians to identify potentially eligible participants, let them know about the study and, if they are interested, ask if a researcher may contact them. Local researchers within the involved health organisation will also screen team caseloads and contact potentially eligible participants. A leaflet about the research study, designed by the trial Lived Experience Advisory Panel, was ethically approved for distribution to potential participants. Study researchers will use all contact details provided to contact potential participants, and offer as many meetings or as much time as a participant requires to understand the study and decide if they want to take part.

Additional strategies to help with participant recruitment were implemented following ethical approval for an amendment to the original trial protocol. Please see Additional file 1: Appedix 1 for details of all protocol amendments:A poster and revised leaflet for potential participants, inviting people to either contact their clinical team or contact the study researchers directly for more information about the study if they wishPermission to display leaflets and posters in other local services (e.g. local day centres) where they may be seen by potential participantsPermission for study researchers to be present at clinic waiting rooms (with clinicians’ agreement) to be on hand to talk to potential participants who would like to hear more about the studyPermission to send group mail-outs with information about the study to service users, where consistent with local services’ consent to contact procedures.

## Assignment of interventions: allocation

### Sequence generation {16a}

Following screening and baseline assessments, eligible participants will be randomised to a treatment group or a control group. We will use block randomisation stratified by site. We will use a web-based randomisation and clinical data management system for recording CRF data (Red Pill), which is provided by a company called Sealed Envelope Ltd. Sealed Envelope has been assessed by PRIMENT Clinical Trials Unit (CTU) to ensure that adequate processes are in place and are being followed for quality management, software development and data security purposes. The Red Pill service has been inspected by MHRA for GCP compliance, and there is a Master agreement and Data Processing agreement in place between UCL and Sealed Envelope to ensure compliance and agreement with clinical trial regulations and data protection laws. Any data that is collected that contains Personal Identifiers such as name, address and NHS numbers will be stored in UCL Data Safe Haven which has been certified to the ISO27001 information security standard and conforms to NHS Digital’s Information Governance Toolkit. Any data that is to be shared outside of UCL will be anonymised and PRIMENT CTU guidance on data sharing will be followed.

### Concealment mechanism {16b}

Only non-blind members of the trial team will be set up with investigator accounts on the trial Sealed Envelope Red Pill database, which makes participants’ allocation status visible and generates email notifications of new randomisations. Blinded study researchers will not be given this investigator access and thus be unable to see participants’ allocation status on the trial database. Randomisations are generated by an algorithm in the Sealed Envelope Red Pill system, so none of the study team have any knowledge of future allocations. Likewise, block sizes for randomisations are known only to the Sealed Envelope system and the lead statistician.

### Implementation {16c}

Group allocation will be generated through Sealed Envelope by the non-blind Trial Manager or trial administrator who will then communicate to participants, clinical teams and Community Navigators the group allocations.

## Assignment of interventions: blinding

### Who will be blinded {17a}

Participants and care providers cannot and will not be blind to participants’ allocation status. Study researchers will be blinded to participants’ allocation status. For data analysis, groups will be labelled only as 1 and 2: the study statistician and health economist who analyse the trial data will be blind to which group is which. The trial manager, trial administrator, peer researcher and the Chief investigator will not be blinded. They will let participants know their allocation status; oversee reporting of serious adverse events, collect process data from the Community Navigators and conduct qualitative interviews for the qualitative sub-study. These researchers will not conduct follow-up interviews with participants, to ensure the researcher-blind integrity of outcomes data.

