#### Primary outcome statistical analysis

The primary analysis of the PHQ-9 score at 8 months follow-up (end-of-treatment) comparing intervention and control groups will use a mixed model (estimated using REML, with the Kenward-Roger adjustment) to perform an individual-level analysis and will follow guidance [41] in adjusting for navigator clustering in the intervention arm only (random coefficient model): specifically, each control subject will be treated as a cluster of size 1. This model will also adjust for baseline PHQ-9 score and site using fixed effects. The estimated intervention effect will be reported with a 95% confidence interval and *p*-value. This analysis will use available data only. All modelling assumptions will be checked. In particular, a confirmatory analysis will be performed using the heteroscedastic model [41] which allows the residual variance for intervention and control groups to differ. Withdrawals from the study, loss to follow-up and other missing outcome data will be summarised separately by randomised group. The primary analysis will be a complete case analysis. However, we will investigate whether there are any predictors of missingness. If any are found, these will be included in an adjusted analysis as a supportive analysis.

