#### Secondary outcome statistical analysis

The effect of the intervention on secondary outcomes will be assessed using analogous methods to those used for the primary outcome. Most of the secondary outcomes are numerical and hence will be analysed using a similar model to that used for the primary outcome, whereas the binary outcomes (those derived from PHQ-9) will be analysed using a mixed-effects logistic regression model. *P*-values will not be reported for secondary analyses. The number and type of adverse events will be summarised by study arm.

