QALYS will be calculated using the EQ-5D-5L and appropriate UK tariff as the area under the curve adjusting for baseline [45]. EQ-5D-5L has been shown to be a valid and responsive measure for depression [46] although there is limited evidence for TRD. The use of the EQ-5D-5L is recommended in the National Institute for Health and Care Excellence [47] allowing for comparisons across disease areas. In the Community Navigators feasibility study [7] (noting very small patient numbers), patients in the intervention group had a 0.19 increase in utility compared to 0.05 in the control group, indicated that the EQ-5D-5L may be sensitive to a treatment effect. However, to address potential limitations with the EQ-5D-5L, we will also calculate QALYs using the ReQoL and its published tariff, a measure of mental health-related quality of life.

We will report the mean incremental cost per QALY gained of the Community Navigator programme plus routine care, compared to routine care, over 14 months for all analyses. The denominator and numerator of the incremental cost per QALY gained will be calculated using regression analysis, accounting for baseline, site as a fixed effect and Community Navigator as a random effect. Other potential coefficients for inclusion will be considered as part of a health economics analysis plan signed off before database close. 95% confidence intervals, cost-effectiveness planes and cost-effectiveness acceptability curves will be calculated based on bootstrapped results. Assuming missing at random, we will use multiple imputation using chained equations to account for missing data. We will consider any potential missing not at random effects and sensitivity analyses for any uncertainty. All costs and consequences beyond 12 months will be discounted at a rate of 3.5% in line with NICE guidance.

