### Methods in analysis to handle protocol non-adherence and any statistical methods to handle missing data {20c}

Adherence to intervention will be described, e.g., in terms of the mean (SD) number of sessions attended. In addition, a complier average causal effect (CACE) analysis may be performed to adjust for any non-adherence to the intervention, where adherence to the intervention is defined as attendance at three or more meetings with Navigators. A further analysis may investigate whether there is a dose response effect of the number of Navigator meetings.

Withdrawals from the study, loss to follow-up and other missing outcome data will be summarised separately by randomised group. Potential bias due to missing data will be investigated by comparing the baseline characteristics of participants with and without missing values. Depending on the quantity of missing values, predictors of missingness may be identified. We will then perform a sensitivity analysis that includes these predictors of missingness as covariates in the primary analysis model. Various multiple imputation strategies may also be performed, if deemed appropriate, assuming either “missing at random” (MAR) or “missing not at random” (MNAR).

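### Labels 1 and 2 cannot keep the analysing statistician and health economist blind once Navigator-level data are released for the specified models

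*Protocol article*

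**What the plan says.** Under Who will be blinded {17a}, the protocol article states: "For data analysis, groups will be labelled only as 1 and 2". It adds that "the study statistician and health economist who analyse the trial data will be blind to which group is which". This is a statement about the analysis stage and about the people who carry out the analysis.

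Other sections determine what data those people need:

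- **Primary outcome statistical analysis.** A mixed model adjusts for Navigator clustering in the intervention arm only, and "each control subject will be treated as a cluster of size 1". A confirmatory heteroscedastic model follows, "which allows the residual variance for intervention and control groups to differ".
- **Secondary outcome statistical analysis.** Effects are "assessed using analogous methods to those used for the primary outcome".
- **Measurement of costs and outcomes.** The cost of delivering the programme is built up from activity that Navigators report. The cost and QALY regressions include "site as a fixed effect and Community Navigator as a random effect".
- **Section {20c}.** A complier average causal effect analysis, based on meetings attended, is optional. So is a second use of attendance: "A further analysis may investigate whether there is a dose response effect of the number of Navigator meetings".

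Procedure for unblinding if needed {17b} allows a masked extract of participant characteristics and baseline scores under labels 1 and 2. It foresees unblinding only of the senior trial statistician, on the monitoring committee's advice. The article names no separate unblinded analyst and describes no device to hide the cluster structure.

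**The concern.** Masking an arm label works only if nothing else in the analysis file gives the arm away. Here the cluster variable does, because only one arm has Navigators. Attendance counts and programme delivery costs do the same. The people described as blind are the people who must use these variables.

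Two things are at stake. The first is accuracy: the article claims a safeguard that its own models rule out at the stage to which the claim refers. The second is the set of choices that may still be open when outcome data are analysed:

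- which baseline imbalances are large enough to prompt an adjusted sensitivity analysis ({20a});
- which predictors of missingness enter the supportive analysis (Primary outcome statistical analysis, and {20c});
- whether to impute, by what strategy, and under which missing-data assumption ({20c}).

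If these are settled after Navigator-level data arrive, they are settled by someone who can see arm and outcome together.

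**Working it through.** **Inputs, all from Sample size {14}:** effect 0.4 SD, 90% power, 5% alpha (taken as two-sided), correlation 0.5, attrition 15%, four sites with three Navigators each, 13 participants per Navigator, ICC 0.05, final size 153 per arm.

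**Reproducing the plan's figures**

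1. Unadjusted size per arm: 2 × ((1.960 + 1.282)/0.4)² = 131.3, so 132.
2. Baseline adjustment: 132 × (1 − 0.5²) = 99. Attrition: 99/0.85 = 116.5, so 117.
3. Design effect: 1 + (13 − 1) × 0.05 = 1.6. Intervention arm: 117 × 1.6 = 187.2, so 188.
4. Equal groups: (188 + 117)/2 = 152.5, so 153 per arm.

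The stated figures are reproduced, and nothing below changes them.

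**What the cluster variable would look like**

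- Intervention arm: 4 × 3 = 12 Navigators, with 153/12 = 12.75 participants each at randomisation and 12.75 × 0.85 = 10.8 after attrition.
- Control arm: 153 clusters of size 1 at randomisation, and 153 × 0.85 = 130 after attrition.

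Replacing Navigator names with arbitrary codes does not help, since the label with multi-member clusters is still the intervention arm. Heavier loss does not help either:

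| Retention | Mean Navigator cluster size | Control singletons |
|---|---|---|
| 85% | 10.8 | 130 |
| 70% (assumed) | 8.9 | 107 |
| 50% (assumed) | 6.4 | 77 |

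The pattern would vanish only if every Navigator had at most one participant with outcome data. With 13 participants and independent 85% retention, the chance of this for one Navigator is 0.15¹³ + 13 × 0.85 × 0.15¹² ≈ 1.5 × 10⁻⁹. For all 12 it is that figure to the twelfth power, about 10⁻¹⁰⁶, which is effectively zero.

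**Which analyses are affected**

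- Primary model: it needs the cluster variable, and the analyst must also attach the Navigator random coefficient to one particular label.
- Secondary outcomes: analogous models, so the same variable.
- Health economics: the ground is separate from the PHQ-9 model. Delivery cost arises in one arm only, and Navigator is a random effect in the cost and QALY regressions.
- Complier and dose-response analyses: attendance exists in one arm only, but these analyses may not be done.
- Baseline and completeness extract in {17b}: no Navigator variable is described as part of it, so labels 1 and 2 can still mask allocation there.

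**The case against.** A reader might infer more than the documents support, and several points limit the problem.

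- **That analysts are unblinded as soon as any dataset is opened.** Not supported. The {17b} extract can remain masked; blinding fails when Navigator identifiers, attendance or costs are supplied.
- **That the plan relies on analyst blinding to keep open choices neutral.** The article gives no such rationale. The safeguard it does state is prespecification: {20a} requires an approved analysis plan before analysis starts, and the health economics section requires its plan to be signed off before database close.
- **That the main result is exposed.** Not supported. The primary model is fixed: REML with Kenward-Roger, adjustment for baseline PHQ-9 and site, complete cases. The open choices are all described as sensitivity, supportive or optional. For the economic analysis, imputation by chained equations under missing at random is already named. Comparing participants with and without missing values does not require knowing which arm is the intervention.
- **That every listed analysis is certain to unblind.** This applies to the primary, secondary and economic models. The complier and dose-response analyses are only possible additions.
- **That the trial will report its blinding untruthfully.** The article makes no commitment on how analyst blinding will be reported.

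It can also be said that a staged data release belongs in an analysis plan or data management plan, neither of which is shown. That is fair as to the procedure, and its absence from an article is not the finding. It does not rescue the sentence in {17a}, which positively claims blinding of those who analyse the data and would still conflict with the specified models.

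**Conclusion.** The blinding statement in {17a} is inconsistent with the models in the same article. From the release of Navigator-level data onward, whoever fits the primary, secondary or economic models can identify the intervention arm. Before that point, blinding is possible.

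Identification is effectively certain for those models under the planned structure of 12 Navigators, and would remain so at half the planned follow-up. It assumes that the named analysts fit the models themselves and that no masking device exists; the article describes none.

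The consequence is limited. Sample size, the prespecified primary estimate and outcome-researcher blinding are not affected. The exposure lies in the supportive and sensitivity choices listed above, and the document gives no basis for putting a size on any bias. The statement should be corrected because it is wrong as written and cheap to put right.

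**What to change.** 1. Reword {17a} so that the statistician and health economist are blind only until Navigator identifiers, attendance and intervention costs are released to them.
2. Release those variables only after both the statistical and the health economics analysis plans are signed off and the open choices are recorded:
   - covariates for imbalance, chosen on baseline data under masked labels 1 and 2 with Navigator variables withheld (pooled data cannot serve, because imbalance between arms cannot be seen without an arm label);
   - predictors of missingness and the imputation model, chosen on pooled data.
3. Describe the analysis as unblinded from the point of release.

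The cost is a change of wording, a staged data release by the trials unit, and a less favourable blinding statement. No additional data are needed.

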### Procedure for unblinding if needed {17b}

On request to the Clinical Trials Unit, data regarding participants’ characteristics and baseline scores on outcome measures can be downloaded from the secure trial database, identified only as Groups 1 and 2, in order to check participant characteristics, data completeness and the balance achieved through randomisation while maintaining blinding. We will follow advice from the Data Monitoring and Ethics Committee and on their advice, the senior trial statistician could be unblinded to look at differences in adverse events or outcomes between groups. The blinded study researchers will ask participants not to reveal whether or not they were allocated to get support from a Community Navigator, but it is possible some participants may reveal their allocation status to the researcher nevertheless. The research team will keep a log of such unblinding incidents and, wherever possible, an alternative researcher who is still blinded will carry out follow-up assessments.

## Data collection and management

### Plans for assessment and collection of outcomes {18a}

Eligibility screening, baseline and follow-up data collection at 8-month end-of-treatment and 14-month follow-ups may be conducted through in-person meetings, video calls or phone calls, as the participant prefers. Four-month and 11-month data will be collected through a self-report online form or phone or video call only. The trial administrator or trial manager will check screening forms to confirm eligibility criteria are met before initiating randomisation through the trial electronic randomisation database. Checks of data completeness and accuracy will be made periodically by the Trial Manager or administrator, supported by the Clinical Trials Unit.

All study researchers will be trained in Good Clinical Practice (GCP) and will receive bespoke training from the Trial Manager and senior study researchers in conducting participant recruitment, including assessing capacity to consent, and study data collection measures. This will involve role play practice using measures with members of the study Lived Experience Advisory Group.

Data collection Case Record Forms are available from the corresponding author on reasonable request.

### Plans to promote participant retention and complete follow-up {18b}

Participants’ decisions to withdraw from (a) the study intervention and (b) the trial will be recorded separately. Where a participant decides to disengage from seeing the Community Navigator before the scheduled end of the programme, the study research team will seek permission to continue to contact the participant to collect outcomes data at follow-up points. If a participant asks to withdraw from the research study, the research team will clarify whether the person (a) just wants no more contact from the researchers, or (b) wishes to withdraw their participation completely, including deleting any data previously collected. If the participant just wants no further contact with the researchers, the study team will retain data collected up to that point and collect data from patient records in accordance with the person’s consent.

Overdue follow-ups will be tracked using the study database. In the case of overdue follow-up visits, reasonable attempts will be made to contact the participant. These will include trying all contact routes provided by the participant and contacting the referring clinician.

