### Trial design {8}

This is a researcher-blind, parallel group randomised controlled superiority trial with two arms. Eligible participants will be randomised in a 1:1 allocation ratio to receive either support from a Community Navigator in addition to routine care (treatment arm), or a booklet with information about local groups and resources plus routine care (control group).

Assessments will be conducted by blinded researchers at the time of consent (baseline) and at two main outcome points: 8-month (end-of-treatment) and 14-month (6 months after end-of-treatment). Baseline measures will be collected at the screening visit, or may be completed if necessary in subsequent meetings, within a maximum of 4 weeks from taking consent. Additional depression and loneliness ratings will be collected through a self-completed online form or through a phone or video call with a study researcher at 4 and 11 months. These additional 4- and 11-month data collection points will be used in additional analyses exploring mediating effects of loneliness on depression (see section “Methods for additional analyses (e.g., subgroup analyses) {20b}”).

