### Criteria for discontinuing or modifying allocated interventions {11b}

The intervention is designed to be delivered flexibly, in a personalised way to meet individual participants’ needs and help them attain personal goals. Participants may choose to stop meeting their Community Navigator at any point during the intervention, and attendance at group “meet-ups” is also voluntary.

A participant may be withdrawn from trial treatment whenever continued participation is no longer in the participant’s best interests, but the reasons for doing so must be recorded.

Decisions to withdraw a participant from the trial intervention will be made ultimately by the site Principal Investigator, following consultation with the involved clinical team, and recorded in the participant’s case record form.

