### Strategies to improve adherence to interventions {11c}

Community Navigators will use all available contact details held by the mental health team to contact participants. They will ask participants about their preferred contact methods and use these wherever possible. They will be as flexible as possible about the time and date of meetings and will seek to rearrange meetings in the event of participants cancelling or not attending meetings; keeping the invitation to participate open throughout the study intervention period.

In order to monitor intervention content and adherence, unblind members of the research team will collect brief information from Community Navigators about meetings with participants, which will be logged in the trial database. This will allow us to describe the number of sessions and meet-up groups attended by each participant and whether or not a participant was treated per protocol (at least three individual sessions).

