## Statistical methods

### Statistical methods for primary and secondary outcomes {20a}

A Statistical Analysis Plan will be finalised and approved prior to commencing analysis. The analyses and subsequent reporting will be guided by the CONSORT recommendations [40]. Analyses will be performed on a modified intention to treat basis, in which participants will be analysed according to their allocated group using all available data for a given outcome and time-point. A CONSORT diagram will be presented to provide a detailed description of participant numbers at each time-point during the trial.

The baseline demographic and clinical characteristics of the participants will be presented in a table summarised separately by study arm. Categorical variables will be reported as counts and percentages. Continuous variables will be summarised as either means and standard deviations (SD) or medians and interquartile ranges, depending on the distribution of the data. No statistical tests will be performed to assess baseline differences between study arms. Any notable imbalances may lead to additional adjusted sensitivity analyses.

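### Stopping the Navigator triggers a new request for permission to follow up, which only intervention participants can meet, so outcome data may be lost selectively in that arm

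*Protocol article*

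**What the plan says.** All references are to the protocol article.

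- **Plans to promote participant retention and complete follow-up {18b}** opens by keeping two events apart: "Participants’ decisions to withdraw from (a) the study intervention and (b) the trial will be recorded separately". The next sentence sets the trigger, "Where a participant decides to disengage from seeing the Community Navigator before the scheduled end of the programme", and the action: "the study research team will seek permission to continue to contact the participant to collect outcomes data at follow-up points". The section then gives any participant a route out of the research on request, and has overdue follow-ups chased without distinction of arm.
- **Trial design {8}** shows who can meet the trigger. It describes the two arms as "support from a Community Navigator in addition to routine care (treatment arm), or a booklet with information about local groups and resources plus routine care".
- **Criteria for discontinuing or modifying allocated interventions {11b}** makes stopping an ordinary, permitted event: "Participants may choose to stop meeting their Community Navigator at any point during the intervention".
- **Strategies to improve adherence to interventions {11c}** has Navigators rearrange missed meetings, "keeping the invitation to participate open throughout the study intervention period".
- **Statistical methods for primary and secondary outcomes {20a}** says that "participants will be analysed according to their allocated group using all available data for a given outcome and time-point". The primary outcome subsection specifies a complete-case analysis adjusted for baseline PHQ-9 and site.
- **Section {20c}** plans a comparison of baseline characteristics by missingness and a sensitivity analysis with baseline predictors of missingness. Imputation under MAR or MNAR assumptions is optional.

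**The concern.** Participants consent at trial entry, and stopping the Navigator is allowed at any time. Stopping is therefore non-adherence to the programme and not withdrawal of consent to be assessed. The retention section nevertheless ties later outcome collection to a renewed permission. A control participant has no Navigator to leave and is never put to that choice.

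If some of those asked say no, the intervention arm loses outcomes that have no counterpart among controls, and loses them from people selected by a post-randomisation event. Should those people have higher PHQ-9 scores than the rest of their arm, the observed intervention mean is too low and the primary comparison favours the programme. The secondary outcomes collected at the same visits are exposed in the same way. So is the possible CACE analysis, because some who stop early will have attended fewer than three meetings, and those are the non-adherers whose outcomes it needs.

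Baseline variables may not capture this mechanism, since engagement arises after randomisation. An analysis plan cannot recover outcomes that were never collected.

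**Working it through.** **1. Who can meet the trigger.** The trigger in {18b} is a decision to stop seeing the Navigator. Under {8} and the description of the control group, controls get a booklet and routine care. The trigger is therefore specific to the intervention arm. The route for leaving the research altogether, later in {18b}, is open to both arms.

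**2. The plan's own figures (Sample size {14}).** These reproduce and are not in dispute.
- Unadjusted: 2 × (1.960 + 1.282)² / 0.4² = 131.4, so 132 per arm.
- Baseline correlation 0.5: 132 × (1 − 0.25) = 99.
- 15% attrition: 99 / 0.85 = 116.5, so 117. The 15% is not split by arm.
- Design effect: 1 + (13 − 1) × 0.05 = 1.6; 117 × 1.6 = 187.2, so 188 in the intervention arm.
- Equalised: (117 + 188) / 2 = 152.5, so 153 per arm and 306 in total.

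**3. Bias.** The documents give no stopping rate, refusal rate or outcome difference, so these are assumptions:
- p = share of the intervention arm who decide to stop: 10–30%
- q = share of those who decline follow-up when asked: 10–50%
- g = how much worse stoppers score at 8 months than the rest of their arm, in SD: 0.3–0.5. Because the model adjusts for baseline PHQ-9, g should be read as the gap that baseline does not explain.

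Measured from the non-stoppers' mean, the full arm mean is p·g. The mean among those observed is p(1 − q)g / (1 − pq). The bias is the difference:

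bias = p·g − p(1 − q)g / (1 − pq) = p·q·g·(1 − p) / (1 − pq)

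| Case | p | q | g | Extra loss, p × q | Bias (SD) | Share of 0.4 SD |
|---|---|---|---|---|---|---|
| Low | 10% | 10% | 0.3 | 1 point | 0.0027 | 1% |
| Middle | 20% | 25% | 0.5 | 5 points | 0.021 | 5% |
| High | 30% | 50% | 0.5 | 15 points | 0.062 | 15% |
| Nobody declines | any | 0 | any | 0 | 0 | 0 |

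Middle case: 0.20 × 0.25 × 0.5 × 0.80 / (1 − 0.05) = 0.020 / 0.95 = 0.021. In participants, 5 points of 153 is about 8.

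The formula assumes that every decliner would otherwise have given an outcome, and that other attrition is unrelated to stopping. The high case adds 15 points by this route alone, as much as the whole attrition allowance in {14}, so it is a harsh upper end.

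**4. Precision.** Normal-approximation power is Φ(0.4 / √v − 1.96), with v = 0.75 × (1/n_control + 1.6/n_intervention). With 15% loss in both arms, each n is 153 × 0.85 = 130.05 and power is 90.4%. With 1, 5, 10 and 15 points of extra loss in the intervention arm it is 90.2%, 89.4%, 88.1% and 86.7%. This holds the design effect at 1.6 and is not the REML/Kenward-Roger analysis, for which {14} gives 87% at 0.4 SD. It shows only the size of the change. Power is a minor matter here; the issue is bias.

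**The case against.** The strongest reply is that the sentence is there to retain people. It sits under a retention heading, follows a rule that separates leaving the programme from leaving the trial, and can be read as an effort to keep those who assume that the two are the same. That reading of its purpose is fair. It does not change the mechanism: the contact is framed as a request for permission, and only one arm receives it.

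Several stronger readings are tempting but not supported.

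- *That outcome data are in fact lost selectively.* The documents do not say that anyone who stops leaves follow-up, and they give no refusal rate. Only a risk can be claimed.
- *That all non-engagers are affected.* The trigger is a decision to disengage. Under {11c} the invitation stays open, so someone who merely does not attend need not meet it.
- *That the request unblinds assessors.* Under {17a}, "Study researchers will be blinded to" allocation, but named unblinded staff collect process data from Navigators and do not conduct follow-up interviews. Section {17b} adds an unblinding log and, where possible, a replacement assessor. What remains is that {18b} does not say which members of the team make the request.
- *That participants withdrawn from the programme by the site Principal Investigator lose follow-up.* This rests on silence. Section {11b} speaks of withdrawal from treatment, and nothing there ends follow-up.

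The planned safeguards also count. Missing data are summarised by arm, predictors of missingness may enter a supportive analysis, and MAR or MNAR imputation is available. These are partly optional, and the planned predictors are baseline ones, so they reduce the exposure without reliably removing it. The direction is uncertain too, since some may stop because they have improved.

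**Conclusion.** The point holds as a risk. A stated rule makes follow-up after stopping the Navigator a matter for renewed permission, only the intervention arm can meet it, and the complete-case analysis would not reliably correct the loss that could follow.

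Under the assumed ranges the bias is about 0.003 to 0.06 SD, or 1% to 15% of the target, with 0.021 SD (5%) in the middle case. All of this rests on assumed stopping and refusal rates and an assumed outcome gap. It vanishes if nobody declines and reverses if stoppers do better. It would not by itself overturn a clear result, but it is avoidable, and participants in either arm can already leave the research on request. This is a cheap improvement. No stated figure is wrong.

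**What to change.** In {18b}, replace the sentence on early disengagement with:

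> Stopping or being withdrawn from the Community Navigator programme is not withdrawal from the trial; scheduled follow-ups continue under the original consent, in both arms alike, unless the participant asks to stop them.

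Two additions:

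- Any contact prompted by stopping should be made by the unblinded staff already named in {17a}. It should tell the participant that follow-up continues and should not ask for new permission. Forbidding such contact altogether would be a mistake, since people who think they have left the trial could then be lost.
- Requests to stop follow-up should be counted and reported by arm.

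Before the change, check that the consent form, which is not shown, covers follow-up after stopping the programme.

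The cost is a protocol amendment, which under {25} needs approval from the Clinical Trials Unit, sponsor, funder, ethics committee and sites, plus a note to sites. No new data are needed. A few participants may be contacted at follow-up and then decline. At the July 2023 protocol version, recruitment was due to run to April 2024 and the trial to August 2025, so many follow-ups could still benefit.
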